#### Secondary Outcomes Analysis

Separate linear mixed models will be used to examine the effects of the e-coaching intervention on the secondary outcomes, which include the EQ-5D-5L, WHOQOL-BREF, the Cantonese Short Version of the Zarit Burden Interview, SCSES-10, and CD-RISC-10. The models will include treatment conditions (e-coaching 1, e-coaching 2, and Control), assessment time points (baseline, immediately post intervention, and 3 months post intervention), and their interaction (group-by-time) effects as fixed effects. Statistical significance will be defined as alpha levels less than .05.

For the 22-item Carer multidimensional assessment, a logistic mixed model will be used, as the outcome will be binary, with 0 indicating not mild need and 1 indicating mild need. The model will include treatment conditions (e-coaching 1, e-coaching 2, and control), assessment time points (baseline, immediately post intervention, and 3 months post intervention), and their interaction effects (group-by-time) as fixed effects. Statistical significance for this model will also be defined as alpha levels less than .05.

Item-level missing data will be minimized by Qualtrics’s function of validation requiring complete responses. Full information maximum likelihood will be used to use all available data and account for the incomplete data (eg, a participant missing follow-up).

### Sensitivity Analysis

Sensitivity analysis will be conducted using a model additionally adjusted for participants’ demographic characteristics such as sex and age or by restricting the sample to only active participants (eg, those with a number of modules completed greater than the median) to assess whether the findings are robust with alternative modeling and sample analyzed.

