### Randomization

Randomization will be conducted using random permuted blocks of three through an online computer randomization system. Participants will be randomly assigned to one of three groups: (1) the full intervention group, where participants will receive the complete e-coaching with full content (ie, 6 sessions); (2) the need-specific intervention group, where participants will receive tailored e-coaching sessions extracted from the full module (ranging from 2 to 6 sessions) based on individual needs; or (3) the control group, where participants will receive video-based educational information about caregiving for 6 weeks.

To maintain allocation concealment, the randomization sequence will be generated prior to participant recruitment and will be securely stored by the research team leader. This approach ensures that those enrolling participants cannot foresee group assignments, thereby minimizing selection bias. In terms of implementation, the intervention will be delivered through an e-platform accessible to participants. This platform will facilitate the distribution of content and support participant engagement throughout the study period. Outcome assessors will be blinded to group assignments to minimize the potential bias in outcome measurement. Participants will be informed that they may not know which group they are assigned to, and they will be encouraged to focus on their personal experiences with the content provided.

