### Intervention

#### e-Coaching Intervention (1 and 2)

The experimental group receives an e-coaching intervention based on LiCBT, lifestyle intervention, and interpersonal effectiveness. This program is designed to operate on an e-platform individually in an interactive, story-based, and self-directed format. It consists of 6 weekly sessions, each lasting about 10 to 30 minutes. Intervention group adherence will be the number of assigned modules completed by the participants. In between each session, participants are assigned home practices to further reinforce the skills learned. e-Coaching 1 will include all content listed in Table 2. e-Coaching 2 will include content tailored to the specific needs of carers, which will be identified using the 22-Item Carer Multidimensional Need Assessment, covering 5 domains of needs, including physical health, mental health, social support, caregiving needs, and caregiving ability (Table 3). This approach ensures that each participant in e-coaching 2 receives more focused material that directly addresses their specific needs.

**Table 2. T2:** Session plan of e-coaching intervention group.

Session	Content and activity	Home practice
Carer online self-directed platform	Introduction of the relationship between online self-directed content and the situation of carer Mindfulness practice	Nil
Lifestyle intervention	Healthy lifestyle Mindfulness practice (standing) Mindfulness practice (stretch)	Mindfulness practice Healthy lifestyle planning
Sleep	Myths about sleep Sleep cycles and hygiene Mindfulness and breathing relaxation practice	Mindfulness practice Breathing relaxation practice Sleep hygiene
Family relationships and communication	Unspoken rules in families Communication skills in the family Mindfulness practice	Mindfulness practice Identify unspoken rules in families Improving communication patterns with family members
Emotion regulation	Identify different emotions Understand emotion mechanism Regulate negative emotion	Mindfulness practice Accumulate positive emotions
Respite time for carers	What is respite service, and why does it matter? Planning respite Mindfulness practice	Mindfulness practice Planning respite time
Caregiving skills for the older adults	Educational content on information, resources, and skills of caregiving for older adults	Nil

**Table 3. T3:** Domains of carer’ needs and e-Coaching modules assigned.

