#### Control Group

On the other hand, the placebo-controlled group attends 6 weekly online sessions that primarily provide video-based educational information in a self-directed format on the same e-platform. The focus of the content will be on practical caregiving skills and promoting general well-being, rather than targeting any particular psychological or mental health–related factors directly. The control group will include all content listed in Table 4. The total duration of the control group lasts about 50 minutes. Control group adherence will be the number of videos completed by the participants. The control condition is designed as an “information-only” educational comparator, reflecting standard educational resources typically accessible to caregivers in the community. It does not include the interactive e-coaching component or structured home practice and does not overlap with the content provided in the intervention arm. This approach allows us to test the intervention materials and evaluate the added value of interactive e-coaching and guided self-help practice over standard educational materials.

**Table 4. T4:** Topics and content of control Group.

Topics	Content
Caregiving experience	Video regarding sharing of other carers’ experiences.
Introduction to knowledge of aging-related health issue and pain management	Videos of early detection of dementia and emotional problems. Videos address strategies for managing and alleviating chronic pain in older adults.
Caregiving resources	Videos of community support resources, including hotline, respite, equipment rental services, useful mobile apps, and support network of community centers.

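### The example rule for active participants counts completed modules without regard to how many were assigned, so it mixes adherence with assigned dose and selects differently by arm

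*Protocol article*

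**What the plan says.** The Sensitivity Analysis section offers two variations on the main model: adding demographic covariates, or "restricting the sample to only active participants (eg, those with a number of modules completed greater than the median". The stated purpose is "to assess whether the findings are robust with alternative modeling and sample analyzed".

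The Randomization section sets the assigned amount of material. In the full intervention group, "participants will receive the complete e-coaching with full content (ie, 6 sessions". The need-specific group receives "tailored e-coaching sessions extracted from the full module (ranging from 2 to 6 sessions) based on individual needs". The e-Coaching Intervention section says that these needs are ones "which will be identified using the 22-Item Carer Multidimensional Need Assessment", and Table 3 maps the five need domains to modules.

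The control arm "attends 6 weekly online sessions that primarily provide video-based educational information in a self-directed format".

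Adherence is defined separately by type of arm, as a count each time. For the two e-coaching arms: "Intervention group adherence will be the number of assigned modules completed by the participants". For the control arm: "Control group adherence will be the number of videos completed by the participants". Neither count is divided by the number assigned.

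**The concern.** A count of completed modules measures adherence only among people who were assigned the same number. Here the number is constant in e-coaching 1, varies with need in e-coaching 2, and is in a different unit in the control arm. A cut on the raw count therefore sorts carers partly by what they were given. In e-coaching 2 it favours those with more need domains, because they were assigned more modules.

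The restricted analysis is meant to show whether the findings hold among carers who engaged with the material. If the rule keeps most of one active arm and few of the other when both behave alike, the restricted contrasts differ from the main ones partly because need profiles differ. Agreement or disagreement with the main result then becomes hard to interpret.

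**Working it through.** **Inputs.** Assigned sessions: 6 in e-coaching 1 and 2 to 6 in e-coaching 2 (Randomization). Domain-to-module map: Table 3. Control unit: videos, number not stated (Control Group). Planned size: 80 per arm (Sample Size Estimation). The article gives no figure for the size of the active subset, no completion rates and no prevalence of need domains.

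**Step 1: reproduce the stated 2 to 6 range.** For each combination of the five domains, count the distinct modules ticked in Table 3, leaving out the introduction, which everyone receives.

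| Need domains | Combinations | Modules assigned |
|---|---|---|
| 1 | 5 | 2, 2, 2, 3, 3 |
| 2 | 10 | 3 to 5 |
| 3 | 10 | 4 to 6 |
| 4 | 5 | 5, 5, 6, 6, 6 |
| 5 | 1 | 6 |

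The range matches the article. Single-domain carers get 2 modules (physical health, social support, caregiving needs) or 3 (mental health, caregiving ability). Lifestyle comes only from physical health and family relationships only from social support. All 6 modules therefore require both of those domains plus at least one of the other three: 2³ − 1 = 7 of the 31 combinations.

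**Step 2: median taken across arms.** The rule keeps a carer if completed > m. Take m = 3 as an illustration:
- e-coaching 2, one domain, everything completed: 2 of 2 or 3 of 3, which is 100%. Neither 2 > 3 nor 3 > 3 holds, so the carer is excluded.
- e-coaching 1, 4 of 6 completed: 4/6 = 67%. 4 > 3 holds, so the carer is kept.

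The same exclusion of fully adherent single-domain carers occurs for any m of 3 or more.

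**Step 3: arm-specific medians in an arm with a fixed assignment.** Take e-coaching 1 with 80 carers, all counted. If 41 complete all 6, the 40th and 41st ordered values are both 6, so m = 6. No count exceeds 6, and nobody is kept. If exactly 40 complete all 6, the 40th value is at most 5, so m ≤ (5 + 6)/2 = 5.5, and those 40 are kept. One more full completer takes the subset from 40 to 0. The same holds in the control arm for videos, if every control is assigned the same number.

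**Step 4: how unequal the selection could be.** A simulation used 80 per arm and identical behaviour in all arms. Each carer completes everything with probability q, and otherwise a lower count drawn uniformly. Assumptions not in the article: q = 0.67, each need domain present in 20% or 40% of carers, and 3 or 6 control videos. The introduction was counted as a module (7 against 3 to 7).

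| Median used | e-coaching 1 kept | e-coaching 2 kept | Control kept |
|---|---|---|---|
| All three arms | 67–81% | 6–59% | 0–43% |
| Two e-coaching arms | 70–75% | 16–20% | not restricted |
| Arm-specific | 0% | 41% | 0% |

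Under the three-arm median, only 9–80% of the e-coaching 2 carers who completed everything were kept. At q = 0.5, arm-specific medians kept 23–27% of e-coaching 1 and 23–30% of control, so emptying an arm does depend on the completion rate.

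**The case against.** The best defence is that the rule is introduced as an example, in a supporting analysis, in a journal article whose analysis plan is not shown. Whether the median is pooled, what the denominator is and where the threshold lies may be settled there. That stands, and none of those details is raised here as missing. What remains is that the one criterion the article states does not suit the design the article describes, and that both adherence definitions repeat the raw-count approach.

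A second defence is that adherence is defined separately for the intervention and control groups, and that the rule speaks of modules, which controls do not have. It could be read as restricting only the e-coaching arms and keeping every control. On that reading the control arm is not emptied. The two e-coaching arms are still selected very unequally (second row of the last table), and each is then a selected subset set against an unselected control arm.

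Third, within e-coaching 1 everyone is assigned the same amount, so with its own median the count does track adherence. That is also true. For that arm the remaining issues are the ceiling at the median and the selection on post-randomisation behaviour that any such subset shares.

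A reader might go further and infer that the subset will be empty, or that the analysis tells us nothing about robustness. The documents support neither. An emptied arm needs particular completion rates, which the article does not give. A subset that mixes adherence with dose is harder to interpret but still carries some information.

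**Conclusion.** The point holds for the example rule as stated. The count mixes adherence with assigned dose and need. With a median across arms of 3 or more, fully adherent single-domain e-coaching 2 carers are excluded while e-coaching 1 carers at 67% completion can be kept. With arm-specific medians, a fixed-dose arm keeps nobody if more than half of it completes everything.

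The misclassification follows from Table 3 and the assigned session numbers alone. The percentages kept rest on assumed completion, need prevalence and number of videos, and show only how far the imbalance could go. The 7 of 31 is a count of combinations, not a share of carers.

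The reach is limited. The primary analysis follows intention to treat whatever the adherence, and the covariate-adjusted sensitivity analysis is untouched. No primary estimate, error rate or sample size changes, and it would be wrong to infer that the main result is at risk.

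**What to change.** Replace the example with a share: modules completed divided by modules assigned in each e-coaching arm, and videos completed divided by videos assigned in the control arm. Call a participant active if the share is at least a threshold fixed before analysis. Every full completer then scores 100% in every arm, and a ceiling can no longer empty an arm.

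State that the restricted comparison is non-randomised and supportive, since it still conditions on behaviour after allocation. State also that the share measures adherence, not exposure: 2 of 2 and 6 of 6 both score 100%.

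Optionally, add a complier average causal effect for each active arm against control, which keeps all randomised carers. It answers a different question and assumes that allocation affects the outcome only through reaching the threshold. That is debatable, because carers below the threshold still receive some modules and controls receive content of their own. The assumption should be stated, and the estimate need not replace the restricted analysis.

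The cost is one or two sentences and no new data beyond the counts already planned and the number assigned to each carer. The article describes enrolment as ongoing and expects analyses to be complete by September 2026, so the rule can be set before analysis. The optional estimate adds a little work and a wider interval.

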## Results

The CONSORT (Consolidated Standards of Reporting Trials) flow diagram is presented in Figure 1. This randomized trial was funded for an original project period from January 2023 to January 2028. The enrollment commenced in April 2025 and is ongoing with the expectation of closing the enrollment in May 2026. We anticipate that data analyses will be completed by September 2026.

**Figure 1. F1:**
[figure not shown]
CONSORT (Consolidated Standards of Reporting Trials) flow diagram.

## Discussion

### Principal Findings

The self-directed e-coaching intervention aims to support carers of older adults by addressing their mental health challenges. Existing literature indicates that carers often experience heightened levels of anxiety and depression, which can adversely affect their well-being and caregiving abilities. Our study aims to evaluate the effectiveness of this innovative intervention in reducing symptoms of anxiety, as measured by the GAD-7, and depression, as assessed by the PHQ-9. The hypotheses proposed that participants in the intervention group would demonstrate greater reductions in anxiety and depression scores compared to a control group, as well as improvements in secondary outcomes such as resilience, quality of life, and caregiving burden

### Summary of Findings

Preliminary insights suggest that self-directed e-coaching can be a viable alternative to traditional in-person interventions, addressing barriers that carers often face, such as limited mobility and inflexible schedules [43]. By offering a flexible online format, the intervention provides carers with the opportunity to engage with the material at their own pace, thereby enhancing accessibility and adherence. This aligns with previous findings that highlight the efficacy of internet-based interventions in improving mental well-being among carers [44,45].

The incorporation of LiCBT principles into the e-coaching model is particularly noteworthy. Meta-analyses have demonstrated LiCBT’s effectiveness in reducing psychological distress among carers, and our approach aims to leverage these techniques in a self-directed format [39].

### Strengths and Limitations

The use of a randomized controlled design enhances the rigor of our findings, allowing for robust comparisons between interventions and control groups. This methodological strength increases the reliability of our outcomes and strengthens the generalizability of the results. It can provide deeper insights into the mechanisms of change, although the reliance on self-report measures may introduce biases. Future research should consider incorporating more objective measures, such as behavioral assessments or physiological indicators, to complement self-reported data.

While the self-directed nature of the e-coaching intervention offers significant advantages, it may not suit all carers, particularly those with lower digital literacy or comfort with technology. Addressing these disparities through tailored support and guidance will be crucial for maximizing the intervention’s reach and effectiveness.

The control arm in this study is not dose-matched with the intervention arms in terms of the sessions’ length, which could introduce a limitation regarding attention-related effects. Future studies should therefore include a dose-matched control condition with similar sessions’ lengths to distinguish specific intervention effects from attention-related effects.

### Importance of This Study

This study is critical for advancing carer support, as it fills a significant gap in research on the effectiveness of self-directed interventions tailored for carers. By examining both primary outcomes—specifically anxiety and depression—and secondary outcomes such as resilience, quality of life, caregiving burden, and self-efficacy, we aim to conduct a thorough evaluation of the intervention’s overall impact. These findings will be instrumental in shaping future carer support programs, ensuring that interventions are designed to address the diverse and complex needs of this population.

Furthermore, the expected improvements in secondary outcomes will provide valuable insights into how the e-coaching intervention enhances overall carer well-being. This comprehensive evaluation not only contributes to a deeper understanding of the intervention’s effects but also aids in refining strategies that enhance relevance and effectiveness in clinical practice.

### Future Directions

As we move forward, further research is needed to explore the long-term effects of the e-coaching intervention and its potential mechanisms of change. Future studies should investigate how specific components of the intervention contribute to the observed improvements in mental health outcomes. Understanding these dynamics will be essential for optimizing the intervention and ensuring its sustainability. Moreover, it will be essential to refine the intervention based on participant feedback and outcomes, ensuring that it remains responsive to the evolving needs of carers.

### Conclusions

In conclusion, our study aims to provide valuable insights into the effectiveness of a self-directed e-coaching intervention for carers of older adults. By addressing both psychological symptoms and broader psychosocial factors, we hope to contribute to the growing body of knowledge that informs best practices in carer support and enhances the resilience and well-being of those in this critical role.

### Dissemination Plans

The trial findings will use multiple channels to reach professional and public audiences. The project findings will be disseminated through peer-reviewed journals and academic conferences to help inform efforts to promote community-based family carer support programs in Hong Kong.
